**Table 4 :Timeline for participants in Arm : B**

***- CECT neck + scan of the relevant part would be done in accordance with the institutional standards.**

**#-Investigations will be done as per institutional standards and sos**

****- FACT H&N QOL would be collected at 6, 12,18,24 & 36 months from start of chemotherapy**

******- Blood sample will be collected only at the first 3 month visit.**

# 13 Sample size

## 13.1 Rationale for selection of primary endpoint : 3 year OS

The primary endpoint selected for sample size calculation is 3 year overall survival. The reason for this being

1. In Head and neck cancers majority of events happen in 2-3 years post treatment completion
2. Availability of data from our institute, on the 3 year outcomes of PET-CT negative patients post radical CTRT.

The 3 years overall survival post radical CTRT in PET-CT negative patients is 68.8%~ 69%. The 3 year overall survival of 69% or more is obtained from multiple international studies reporting results of CTRT in stage III-IV head and neck cancers.

| Study name | n | Stages included | 3 year OS |
| --- | --- | --- | --- |
| RTOG 0522 | 891 | Stage III & IV head & neck cancers.  Randomly assigned to receive radiation and cisplatin without (arm A) or with (arm B) cetuximab. | Arm A :72.9% *v Arm B:* 75.8%, respectively; *P* = .32) |
| RTOG 0129 | 743 | Patients had **stage III to IV carcinoma of the oral cavity, oropharynx, hypopharynx, or larynx.** Radiation therapy schedules were 70 Gy in 35 fractions over 7 weeks (SFX) or 72 Gy in 42 fractions over 6 weeks (AFX-C). Cisplatin doses were 100 mg/m^2^ once every 3 weeks for two (AFX-C) or three (SFX) cycles. | 8-year survival, 48% *v* 48%). **The 3 year OS was around 70%** in both arms. |
| DeCIDE | 285 | In this phase 3, open-label trial, subjects with **pathologically confirmed SCCHN; N2/N3 disease without metastases**; no prior therapy; KPS ³ 70%; and intact organ function were randomized to CRT alone (CRT arm) [5 days of D (25 mg/m2), F (600 mg/m2), hydroxyurea (500 mg BID), and RT (150 cGy BID) followed by a 9 day break] or to 2 cycles of IC [D (75 mg/m2), P (75 mg/m2), F (750 mg/m2 day 1-5)] followed by the same CRT (IC arm). | **3 year OS was 75% and 73% in CTRT & IC-CTRT** |
| PARADIGM | 145 | Patients were eligible if their tumour was either **unresectable or of low surgical curability on the basis of advanced tumour stage (3 or 4) or regional-node stage (2 or 3, except T1N2), or if they were a candidate for organ preservation**. Patients were randomly assigned (in a 1:1 ratio) to receive either induction chemotherapy with three cycles of TPF followed by concurrent chemoradiotherapy with either docetaxel or carboplatin or concurrent chemoradiotherapy alone with two cycles of bolus cisplatin. | **3-year overall survival was 73% (95% CI 60-82) in the induction therapy followed by chemoradiotherapy group and 78% (66-86) in the chemoradiotherapy alone group (hazard ratio 1·09, 95% CI 0·59-2·03; p=0·77)** |
| **Mehanna et al** | 564 | In this prospective, randomized, controlled trial, the authors assessed the noninferiority of positron-emission tomography–computed tomography (PET-CT)–guided surveillance (performed 12 weeks after the end of chemoradiotherapy, with neck dissection performed only if PET-CT showed an incomplete or equivocal response) to planned neck dissection in patients with stage N2 or N3 disease. | The 2-year overall survival rate was 84.9% (95% confidence interval [CI], 80.7 to 89.1) in the surveillance group and 81.5% (95% CI, 76.9 to 86.3) in the planned-surgery group. **The 3 year OS is well above 70%.** |

Table 5 : Studies supporting 3 year OS of 69-70% in stage III-IV head and neck cancers post CTRT.

## 13.2 Rationale for interim analysis

The survival benefit shown with adjuvant metronomic studies is limited sample size cohort studies. Hence as the investigators plan to do a study which is powered for an absolute survival improvement of 6% at 3 year in OS.It was decided to have a multiple interim analysis.

## 13.3 Sample size justification

### 13.3.1 Sample size

The primary endpoint for is 3 year OS. The study assumes a 3 year OS in standard arm of 69%. With Type I error of 5% , Type II error of 20%, for a hazard ratio of 0.77, with study duration of recruitment of 9 years, study follow up of 3 years and 5 % lost to follow up the sample size was calculated using fixed design, two-arm trial with time-to-event

outcome (Lachin and Foulkes, 1986) in Rstudio version 3.2.1. The sample size required was 950 patients with analysis done at 485 events. However in view of the large sample size 3 interim analysis were included in this study using Group sequential design sample size with Hwang-Shih-DeCani spending function for time-to-event outcome events. The final **sample size was 1038 patients**. The analysis plan below shows events at each analysis with the decision rules.

**Decision rules**

Upper bound spending computations assume trial continues if lower bound is crossed.

----Lower bounds---- ----Upper bounds-----

Analysis N Z Nominal p Spend+ Z Nominal p Spend++

1st interim 133 -0.75 0.2275 0.0203 2.95 0.0016 0.0016

2nd interim 265 0.13 0.5509 0.0335 2.58 0.0049 0.0044

3rd interim 398 0.91 0.8180 0.0552 2.17 0.0151 0.0118

Final analysis 530 1.69 0.9548 0.0910 1.69 0.0452 0.0322

Total 0.2000 0.0500

+ lower bound beta spending (under H1):

Hwang-Shih-DeCani spending function with gamma = -2.

++ alpha spending:

Hwang-Shih-DeCani spending function with gamma = -4.

Boundary crossing probabilities and expected sample size

assume any cross stops the trial

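### The event count was sized at two-sided 5% but the stopping bounds spend 5% one-sided, so superiority could be declared at a two-sided p of about 0.09

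*Protocol*

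**What the plan says.** Protocol 13.3.1 gives the design inputs as "With Type I error of 5% , Type II error of 20%, for a hazard ratio of 0.77", with a control-arm 3-year survival of 69%, 9 years of recruitment, 3 years of follow-up and 5% loss. Section 13.2 describes the trial as "powered for an absolute survival improvement of 6% at 3 year in OS". For a single-look design, 13.3.1 continues: "The sample size required was 950 patients with analysis done at 485 events". A group-sequential design with three interim looks then raises this to 1038 patients.

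The Decision rules table has looks at 133, 265, 398 and 530 events. Efficacy uses Hwang-Shih-DeCani spending with gamma -4, and futility uses the same family with gamma -2. The efficacy bounds are computed as if futility crossings were ignored (non-binding). The final row is "Final analysis 530 1.69 0.9548 0.0910 1.69 0.0452 0.0322" and the column totals are "Total 0.2000 0.0500": 0.2000 of beta on the lower side and 0.0500 of alpha on the upper side. The protocol nowhere calls the test one-sided or two-sided.

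**The concern.** The lower bounds are futility bounds that spend beta, so the whole 0.05 is spent on the upper side, in favour of metronomic therapy. That makes it a one-sided 5% rule. Its final critical value of 1.69 is below the 1.96 of a single-look two-sided 5% test, although three earlier looks have already used some of the alpha. If the event count was built on a two-sided 5% test, the two halves of the design rest on different error rates. A final Z between 1.69 and about 2.01 would then be positive by the table and negative at the error rate that sized the trial. This is the primary overall survival decision of a phase III trial.

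**Working it through.** **Inputs.** Power 80%, HR 0.77, control 3-year OS 69% (13.3.1); a 6-point gain (13.2); spending functions and events per look (Decision rules). Allocation of 1:1 is an assumption, since no ratio is stated.

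**1. Which alpha gives 485 events?** With proportional hazards, 69% to 75% gives HR = ln 0.75 / ln 0.69 = 0.7753, which truncates to 0.77. Schoenfeld's formula is events = 4(z_α + z_β)² / (ln HR)², with z_β = 0.842.

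| HR | two-sided 5% (z = 1.960) | one-sided 5% (z = 1.645) |
|---|---|---|
| 0.7753 | 31.40 / 0.0648 = **484.7** | 24.73 / 0.0648 = 382 |
| 0.77 | 31.40 / 0.0683 = 460 | 24.73 / 0.0683 = 362 |

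Two-sided 5% reproduces 485 with the unrounded HR. One-sided 5% falls 21–25% short at either HR.

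The patient number agrees. The Lachin-Foulkes formula at HR 0.7753 gives 957 patients two-sided and 754 one-sided, against the stated 950. This assumes that the 5% loss accrues over 3 years, as no time base is given. Over other bases (no loss to 5% per year) the two-sided range is 904–1068 and the one-sided range 712–841.

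**2. Which alpha gives the printed bounds?** Cumulative spending is α(t) = α(e^{4t} − 1)/(e^4 − 1). With α = 0.05 and t = 0.25, 0.5, 0.75, 1, the increments are 0.0016, 0.0044, 0.0118 and 0.0322, which is the printed column. Recursive integration with a non-binding lower bound gives:

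| | upper Z | lower Z | inflation |
|---|---|---|---|
| Printed | 2.95, 2.58, 2.17, 1.69 | -0.75, 0.13, 0.91, 1.69 | 530/485 = 1.093 |
| One-sided 0.05 | 2.947, 2.582, 2.168, 1.693 | -0.747, 0.128, 0.908, 1.693 | 1.094 |
| One-sided 0.025 | 3.155, 2.818, 2.439, 2.014 | -0.587, 0.355, 1.186, 2.014 | 1.087 |

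Only one-sided 0.05 matches. The chain is then visible: 1.094 × 485 = 530.5 events and 1.094 × 950 = 1039 patients (stated: 530 and 1038). A two-sided event count was multiplied by the inflation factor of a one-sided 5% sequential design.

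**3. How does the printed rule behave at 530 events?**

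- No effect: efficacy crossing 5.0%, or 4.6% if futility stops are obeyed.
- Final look: two-sided p = 2 × 0.0452 = 0.090. The largest winning HR is exp(−2 × 1.69/√530) = 0.863.
- Power with futility obeyed: 88% at HR 0.7753 and 89% at HR 0.77. Total lower-bound crossing is 12.3% and 10.9%, against a printed 0.2000.
- The alternative that the table actually assumes: the drift is (1.645 + 0.842) × √1.094 = 2.60, so ln HR = −2 × 2.60/√530.5 = −0.226 and HR = 0.798. That corresponds to 69% rising to 0.69^0.798 = 74.4%, an effect stated nowhere in the protocol.
- Hand check at the first look: under HR 0.77 with 133 events the mean of Z is 0.2614 × √(133/4) = 1.507, so the chance of falling below −0.75 is Φ(−2.257) = 0.012. The printed beta spend is 0.0203.

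**4. Bounds spending 0.025.** The one-sided 0.025 row above needs 1.087 × 485 = 527 events. At the printed 133/265/398/530 events its power is 80.2% at HR 0.7753 and 82.3% at HR 0.77. Its false-positive rate is 2.5% with futility ignored.

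**The case against.** The protocol states a 5% type I error and the table spends exactly 0.0500, so no printed error rate is breached. The 2.5% comparator is inferred from 485 events, and that inference is exact only at HR 0.7753. At the printed 0.77 the two-sided count is 460, about 5% short, and at the 6.5-point gain in section 7 (HR 0.757) it is 407. One-sided 5% may have been intended throughout, in which case the bounds are right and the event count is merely generous. Higher power and fewer false futility stops do no harm. It can also be argued that only the efficacy bounds need changing: keeping the printed interim futility bounds gives 81.6–83.5% power.

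It stands that the sidedness is inferred and that the HR is loosely stated. Neither rescues the plan. Every one-sided count misses 485 by more than the corresponding two-sided count does. If one-sided 5% was meant, 382 fixed and about 418 sequential events would suffice at HR 0.7753, so 530 is over 100 deaths too many and the section is still inconsistent. The futility bounds in the fix are what the protocol's own spending functions give once alpha is 0.025. The printed ones belong to an HR of 0.798.

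**Conclusion.** Wrong as written. No single type I error produces both the 485/530 events and the printed bounds. Against the two-sided 5% that sized the trial, the rule doubles the one-sided false-positive rate (5.0% against 2.5%) and accepts a final two-sided p of about 0.09, an observed HR of 0.863 instead of 0.839 (exp(−2 × 2.014/√530)). The stated 20% type II error is not a property of the printed rule, whose power is 88–89%.

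The conclusion assumes 1:1 allocation and proportional hazards, and reads the effect as 69% to 75%. The sidedness finding does not hinge on the last of these, because one-sided counts miss by 21–25% at HR 0.7753 and 0.77 alike. This must be settled before any unblinded interim look.

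**What to change.** State in 13.3.1 that the type I error is two-sided 5% (one-sided 2.5% for efficacy), and replace the Decision rules table with bounds that spend 0.025 in total, keeping the gammas and the looks:

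| Events | Lower Z | Upper Z | Nominal one-sided p (upper) |
|---|---|---|---|
| 133 | -0.59 | 3.16 | 0.0008 |
| 265 | 0.36 | 2.82 | 0.0024 |
| 398 | 1.19 | 2.44 | 0.0074 |
| 530 | 2.01 | 2.01 | 0.0220 |

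Give the unrounded HR (0.7753, for 69% to 75%) so that the 485 can be reproduced. The cost is one protocol amendment covering one table and a sentence or two. No extra patients or events are needed, and power becomes 80–82% at HR 0.7753–0.77.

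If the sponsor did intend a one-sided 5% test, the protocol must say so and justify it, and the event count must be re-derived on that basis (about 418 sequential events at HR 0.7753). The total of 1046 in the concept sheet, against 1038 in 13.3.1, is a separate discrepancy that the same amendment can settle.

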# 14 Recruitment

All patients post radical chemoradiation in Head and neck medical oncology OPD ( general, private or at ACTREC) would be informed about the study and if they are willing would be screened for the same.

# 15 Allocation of arm

## 15.1 Sequence generation

Stratified randomization would be done. The stratification would be for site of tumor (oropharynx versus larynx versus hypopharynx), T stage ( T1-2, T3 , T4) and N stage ( N0, N1, N2-N3). The randomization sheet would be computer generated. Twenty seven sheets would be generated.

## 15.2 Allocation concealment mechanism

These sheets would be maintained within the protocol room. The trial PI, Co-I and trial coordinators won't have access to it. One of the trial coordinators of other head and neck medical oncology study would be entitled with its responsibility.

## 15.3 Implementation

Investigators or trial coordinators would email the person incharge about the patient's details ( site of tumor, T stage and N stage). The person incharge of the randomization sheet would issue a randomization number and the arm.

# 16 Data collection methods

The data of the study would be collected in a pre designed case record form. The data will be filled in excel sheets and then would be transferred in SPSS and/or R studio for requisite analysis.

# 17 Data monitoring

The institutional data monitoring and safety board (DSMB) will be responsible for oversight of the data.

# 18 Harms

An ADVERSE EVENT (AE) is any untoward medical occurrence in a patient or clinical investigational subject administered a pharmaceutical product and which does not necessarily have a causal relationship with this treatment. An AE can therefore be any unfavourable or unintended sign (including an abnormal laboratory finding), symptom, or disease temporally associated with the use of a medicinal investigational product, whether or not considered related to the medicinal product (see below).

Adverse events include the following

All suspected adverse drug or device reactions

1. All reactions from drug or device – overdose, abuse, withdrawal, sensitivity, toxicity or failure of expected pharmacological action (if appropriate)
2. Apparently unrelated illnesses, including the worsening (severity, frequency) of pre-existing illnesses
3. Injury or accidents.
4. Abnormalities in physiological testing or physical examination that require clinical intervention or further investigation (beyond ordering a repeat examination)
5. Laboratory abnormalities that require clinical intervention or further investigation (beyond ordering a laboratory test)
6. Any untoward event that occurs after the protocol-specified reporting period which the Investigator believes may be related to the drug or device.

**AEs are not required to be reported unless they meet SAE criteria.**

A SERIOUS ADVERSE EVENT (SAE) is any untoward medical occurrence that at any dose:

1. results in death,
2. is life-threatening (i.e. the subject is at risk of death at the time of the event),
3. requires inpatient hospitalisation or prolongation of existing hospitalisation,
4. results in persistent or significant disability or incapacity,
5. is a congenital anomaly/birth defect,
6. other important medical events which, in the opinion of the investigator, are likely to become serious if untreated, or as defined in the protocol

NOTES:

(i) The term “life-threatening” in the definition of “serious” refers to an event in which the patient was at risk of death at the time of the event; it does not refer to an event which hypothetically might have caused death if it were more severe.

(ii) Important medical events which may not be immediately life-threatening or result in death or hospitalization but which may jeopardize the patient or may require intervention to prevent one of the listed outcomes in the definition above should also be considered serious.

# 19 Auditing

The trial data will be audited at 6 monthly intervals to monitor the participant enrolment, consent, eligibility, and allocation to study groups; adherence to trial interventions and policies to protect participants, including reporting of harms; and completeness, accuracy, and timeliness of data collection. An independent auditing body will be tasked with this purposed which has been identified by the data safety and monitoring body (DSMB).

# 20 Research ethics approval

This protocol and the template informed consent forms contained in Appendix will be reviewed and approved by the institutional IRB with respect to scientific content and compliance with applicable research and human subjects regulations. The protocol, site-specific informed consent forms (local language and English versions), participant education and recruitment materials, and other requested documents—and any subsequent modifications — also will be reviewed and approved by the IRB. Subsequent to initial review and approval, the IRB will review the protocol at least annually. The Investigator will make safety and progress reports to the IRB at 12 monthly intervals and within three months of study termination or completion. These reports will include the total number of participants enrolled and summaries of each DSMB [data safety and monitoring board] review of safety and/or efficacy.

# 21 Protocol amendments

Any modifications to the protocol which may impact on the conduct of the study, potential benefit of the patient or may affect patient safety, including changes of study objectives, study design, patient population, sample sizes, study procedures, or significant administrative aspects will require a formal amendment to the protocol. Any and all such amendments will be communicated to the institutional IRB for review and approval. Administrative changes of the protocol are minor corrections and/or clarifications that have no effect on the way the study is to be conducted. These may be communicated to the IRB at the investigator's’ discretion.

# 22 Consent

Patients will be given the patient information sheet by the trial investigators / nurses. The purpose and reasons behind the study will be communicated to the patient. All patients will be provided with a copy of the written informed consent as well as the patient information sheet. Consent will be recorded on as per institutional IRB guidelines.

# 23 Confidentiality

All study-related information will be stored securely at the study site. All participant information will be stored in locked file cabinets in areas with limited access. All laboratory specimens, reports, data collection, process, and administrative forms will be identified by a coded ID [identification] number only to maintain participant confidentiality. All records that contain names or other personal identifiers, such as locator forms and informed consent forms, will be stored separately from study records identified by code number. All local databases will be secured with password-protected access systems. Forms, lists, logbooks, appointment books, and any other listings that link participant ID numbers to other identifying information will be stored in a separate, locked file in an area with limited access.

# 24 Access to data

TMH : The Principal Investigator and Co investigators will be given access to the data sets. Project data sets will be housed on the project specific database created for the study, and it will be password protected.

Other centers : The Data Management Coordinating Center will oversee the intra-study data sharing process, with input from the Data Management Subcommittee. All Principal Investigators will be given access to the cleaned data sets. Project data sets will be housed on the project specific database created for the study, and all data sets will be password protected.

# 25 Ancillary & post trial care

Patients metronomic treatment and supportive care cost would be beared by the study budget . Patients will be treated further in accordance with institutional guidelines. In addition in the event of intolerable side effects or disease progression palliative radiotherapy or chemotherapy will be used for their treatment if feasible. These costs will not be reimbursed for the patient as they are standard of care for such patients. Patients will be treated for trial related adverse events in the hospital. Compensation for adverse events will be provided in accordance with institutional standards.

# 26 Dissemination policy

The trial results will be submitted for publication in international peer reviewed journals and presented at national/international conferences. No publication restrictions will be imposed by trial sponsors. All co investigators will be given authorship on the manuscript as well as on any abstract that are reported in national/international conferences. The principal investigator will take either the role of the corresponding author or the first author positions as decided mutually among the investigators. Authorship criteria for other publications stemming from the study will be decided as per the relative contributions and existing institutional guidelines. The contribution of all investigators will be acknowledged in such manuscripts if they are not eligible for authorship. In addition the grant giving organizations will also be acknowledged in all publications.

